# Effects of a multimodal exercise intervention on physical and cognitive functions in patients with chronic low back pain (MultiMove): study protocol for a randomized controlled trial

**DOI:** 10.1186/s12877-021-02093-1

**Published:** 2021-03-02

**Keywords:** Motor control, Dance, Gait variability, Dual task, Functional near-infrared spectroscopy

## Abstract

**Background:**

Chronic low back pain (CLBP) is a common medical condition in adults over the age of 50. It is associated with severe disability, ranging from physical impairments to psychosocial distress. Since current treatments provide only small to moderate short-term effects, alternative interventions are required, whereby guidelines recommended multimodal approaches. Dancing can be considered as an inherently multimodal approach, as it requires a combination of physical and cognitive functions. Furthermore, it has already been applied effectively in neurorehabilitation. Therefore, it seems promising to merge a dance-therapeutic component together with motor-cognitive, strength and flexibility exercises in a novel multimodal treatment (MultiMove) to target the impaired everyday mobility and cognition of CLBP patients. The aim of this study is to analyse specific physical, cognitive and psychosocial effects of MultiMove in CLBP patients.

**Methods:**

A prospective, two-arm, single-blinded, randomized controlled trial will be conducted with an estimated sample size of 100 CLBP patients, assigned to either the MultiMove group or a control group. The intervention group will receive MultiMove twice a week for 60 min each over a period of 12 weeks. The primary outcome will be the mobility and function of the lower extremities assessed by the Timed Up-and-Go Test. Secondary outcomes comprise further physical and physiological functions (e.g. gait variability and haemodynamic response in the prefrontal cortex during motor-cognitive dual tasks), subjective health state (e.g. disability in daily life), executive functions (e.g. cognitive flexibility) and psychosocial aspects (e.g. kinesiophobia). Measures will be taken at baseline, after the intervention and at a 12-week follow-up. It is assumed that MultiMove improves the mentioned outcome parameters.

**Discussion:**

The combined assessment of changes in physical and cognitive functions as well as neuropsychological aspects in response to MultiMove will allow a better understanding of the motor-cognitive adaptations induced by multimodal exercises in CLBP patients. The specific conclusions will lead to recommendations for the conservative treatment approach in this clinically relevant patient group.

**Trial registration:**

German Clinical Trial Register (ID: DRKS00021696 / 10.07.2020), https://www.drks.de/drks_web/navigate.do?navigationId=trial.HTML&TRIAL_ID=DRKS00021696

## Background

Low back pain (LBP) is a frequent medical condition and major economic health issue in Germany with a lifetime prevalence of around 85% in the population [1]. In a study considering the global burden of diseases, LBP was classified as the condition highest in terms of disability. Furthermore, it was shown that the prevalence increases with age and that the chronic type of LBP (CLBP, with and without leg pain) was associated with the most severe disability [2]. Thereby, CLBP is defined as pain in the lumbar region of the spine lasting for at least 3 months [3]. Although, only a small percentage of LBP patients develop CLBP [3, 4], they are responsible for the majority of costs associated with LBP caused by recurrent health care consultations, occupational incapacity and early retirement [5–8]. Degenerative changes in the lumbar spine are strongly associated with CLBP [5, 9]. However, in most of the cases they cannot sufficiently explain the underlying pain mechanisms and the related impairments [4, 10–12].

On a physical level, CLBP patients can experience limitations such as insufficient muscular trunk stabilisation and strength [13], as well as a poor static postural control and an altered gait performance [14–17]. Moreover, research indicates that motor-cognitive dual task performance (e.g. walking while performing a cognitive task) is reduced in CLBP patients [14, 18]. This could be explained by the fact that pain can interfere with gait control, e.g. executive functioning [14, 19]. This is consistent with the observation that patients with chronic pain showed reduced cognitive functioning (e.g. executive functions) [20]. These motor-cognitive deficits lead to limitations in daily activities and may provoke an increased risk of falling [13, 19, 21]. Nevertheless, it is essential to consider that also psychological factors like anxiety, depression and/or passive coping strategies affect the development and maintenance of CLBP [4, 22]. In addition, these impairments reinforce each other: e.g. the fear of pain leads to a decreased daily activity level (described as kinesiophobia [23]), contributing to the insufficient muscular stabilisation and disability level [16, 24]. These multidimensional negative experiences impair the patients beyond the chronic pain and contribute to a reduction in health-related quality of life [25, 26].

To address the multifaceted impairments of CLBP, multidisciplinary approaches are recommended [3]. They have shown superior effectiveness in decreasing pain and disability compared to usual care [27, 28]. In this regard, a combination of conservative (e.g. pharmacological, physical, psychological) interventions are applied by specialists of diverse professions [16, 27, 29]. Building on this holistic treatment approach and to further improve the effectiveness, we have designed a novel multimodal exercise intervention (MultiMove) for CLBP patients. MultiMove addresses the described impaired physical (e.g. dynamic postural control, trunk stability), cognitive (e.g. executive functions) and psychological (e.g. kinesiophobia) domains of CLBP, through the combination of three training components.

The basic component of MultiMove consists of a strength and flexibility training, as they have been shown to be the most effective exercise interventions for CLBP patients, so far [30, 31]. To moreover address the impaired dual task performance and the executive functions of CLBP patients, the second component of MultiMove is a motor-cognitive training according to the Life Kinetik® concept [32]. In healthy older adults, this kind of training has already been shown to decrease gait variability as well as reduce fear of falling [33, 34]. Because balance/stabilisation training has been shown to be advantageous for CLBP patients [30], the third component comprises a dynamic balance training using dance-therapeutic elements. Moreover, dance-therapeutic exercises inherently require a combination of motor and cognitive functions (e.g. to remember and execute several partial movements at the same time) and are further associated with social interaction [35, 36]. In combination with the beneficial effects of the motor-cognitive training, this social interaction might help to overcome the kinesiophobia. In line with this, it has been shown that dance interventions improve functional mobility, sensorimotor and endurance performance in healthy adults and elderly [37–39]. Besides, dance interventions might lower gait variability and improve gait speed [40, 41]. Additionally, it has been revealed that dancing is superior to conventional training interventions (involving mainly repetitive physical exercises) with regard to the training-induced brain plasticity in elderly people [42]. Due to these multiple benefits, dance-therapeutic interventions have already been effectively applied in the field of neurological rehabilitation [36, 43–46]. Therefore, extending the approach to the needs of CLBP patients seems promising.

With the combination of these three components, MultiMove is expected to contribute to an improvement in physical and physiological functions (e.g. Timed Up-and-Go [TUG] performance, gait variability, haemodynamic response in the prefrontal cortex [PFC]) as well as cognitive performance [aspects of executive functions]). A reduction in pain as well as an increase in quality of life are assumed to come along with those changes.

### Primary objective

To test the effect of MultiMove on CLBP patients’ physical function (TUG performance) relative to the conventional conservative therapy.

### Secondary objectives

To examine changes in the LBP specific disability (Oswestry Disability Index, ODI) and health-related quality of life (EQ-5D-5L) between groups and over time.To evaluate the specific physical changes induced by MultiMove (gait variability, flexibility, functional exercise capacity and leg extensor muscle power).To analyse if MultiMove induces changes in selected executive functions (inhibitory control, cognitive flexibility) and/or in the haemodynamic response in the PFC during dual task standing and walking in CLBP patients.To determine the potential long-term psychosocial effects (Kinesiophobia, pain coping strategies) provoked by MultiMove.

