##### Coping Strategies Questionnaire

The Coping Strategies Questionnaire is a reliable measure for pain coping techniques [78]. In this study, the German version will be used (CSQ-D) [79]. The CSQ-D comprises 50 items in total. The first 48 items describe different cognitive or behavioural coping techniques (cognitive: diverting attention, reinterpreting pain sensations, coping self-statements, ignoring pain sensations, praying or hoping, catastrophizing; behavioural: increasing activity level, increasing pain behaviours). Participants are asked to rate how frequently they use each of the described coping techniques on a 7-point scale (0 = never, 6 = always). Additionally, two items assess their self-reported overall effectiveness of their strategies. To evaluate the CSQ-D, a score is calculated for each coping technique ranging from 0 to 36 [79].

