### Data analysis and management

Data will be analysed using IBM SPSS 26.0 (SPSS Inc., Chicago, IL). At first, a descriptive analysis will be conducted to identify outliers, distributions and to display the baseline characteristics of both groups (means, proportions, standard deviations). To evaluate the effects of the intervention, data of all patients will be processed, regardless of whether they fully received or dropped out of the intervention (intention-to-treat-analysis). Thereby, data will be analysed until the date of drop out. As a secondary analysis, only the data from the participants who participated at least 80% of the intervention will be included in a per-protocol analysis. Missing data will be imputed using multiple imputation, under the assumption that data are missing at random. Statistical significance level will be set at *p* ≤ 0.05 (1-sided).

In order to analyse differences between the groups at the time points post and follow-up, two ANCOVAs with baseline adjustments will be undertaken (covariates: baseline values and, when required, e.g. age, sex etc.) for all outcome measures. Subsequently, alpha-adjustments will be undertaken. In case the assumptions for the ANCOVA will be violated, mixed models will be used. To further elaborate the outcomes and their interactions, additional parametric or nonparametric statistical analyses will be applied. Exploratory mediation analysis will be performed supplementary.

To preserve the confidentiality, all participants will receive a specific code with which the data will be labelled, while the participants contact data will remain under lock. The collected data will be stored digitally and can only be accessed by the study group. Therefore, the data will be transmitted by one person and checked for correctness by another (transmission errors and plausibility). In this study, no data monitoring committee and interim analysis will be established, because of the minimal risks associated with the intervention. Overall, the data management will be in line with of the European General Data Protection Regulation.

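### The one-sided 0.05 level covers all outcomes, but no favourable direction is stated for the prefrontal haemodynamic response or the eight coping scores

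*Protocol article*

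**What the plan says.** **Test rule.** Under Data analysis and management, "two ANCOVAs with baseline adjustments will be undertaken", one for post and one for follow-up, for every outcome measure. The significance level is 0.05, one-sided. Alpha-adjustments are to follow; no method is named.

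**Objectives.** Under Secondary objectives, the third item asks whether there are changes in selected executive functions and/or "in the haemodynamic response in the PFC during dual task standing and walking in CLBP patients". The fourth asks about long-term psychosocial effects, including pain coping. Neither gives a direction.

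**Predictions.** The Abstract (Methods) lists among the secondary outcomes "gait variability and haemodynamic response in the prefrontal cortex during motor-cognitive dual tasks" and "psychosocial aspects (e.g. kinesiophobia"), and then says: "It is assumed that MultiMove improves the mentioned outcome parameters". The Background expects MultiMove to contribute to "an improvement in physical and physiological functions (e.g. Timed Up-and-Go [TUG] performance, gait variability, haemodynamic response in the prefrontal cortex [PFC"]).

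**Measures.** The fNIRS section records relative oxy- and deoxyhaemoglobin. For the Coping Strategies Questionnaire, "a score is calculated for each coping technique ranging from 0 to 36"; eight techniques are listed, from coping self-statements to catastrophizing. Neither section says which direction is favourable. By contrast, the sections on the Oswestry index, the EQ-5D-5L visual scale and the Tampa scale each say what a high value means.

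**The concern.** A one-sided test rejects in one tail only, so it needs to know which tail. For times, walking distance, pain or disability the answer is obvious or stated. For prefrontal activation it is not: a fall in oxyhaemoglobin during a dual task could be welcome or unwelcome, and the article does not commit itself. The coping techniques are mixed, so a single common direction for all eight is implausible.

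The article therefore prescribes a directional test and predicts improvement while its objectives ask a non-directional question. If the sign is settled only once the estimates are known, a rise and a fall could each be declared significant at the lenient one-sided threshold and described as a benefit. This matters most for the prefrontal response, because the Discussion presents the combination of neuropsychological tests, gait analysis and fNIRS as a major advantage of the study.

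**Working it through.** **1. The plan's own figure, to show that it is not involved.** Sample size section: f = 0.40, alpha 0.05, power 0.95, two groups, two covariates, N = 84. ANCOVA F test with noncentrality N × f² = 84 × 0.16 = 13.44 and 1 and 84 − 2 − 2 = 80 degrees of freedom: power 0.952, and 84 is the smallest N that reaches 0.95. With 15% dropout, 84 / 0.85 = 98.8, so 99 against the stated 100. The figure is reproduced. It concerns the Timed Up-and-Go test and does not bear on this point.

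**2. Is a direction stated?**

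| Outcome | Prediction | Objective | Favourable direction |
|---|---|---|---|
| Oxy-/deoxyhaemoglobin in the prefrontal cortex | Improvement, by name (Abstract, Background) | Changes | Not stated in the Background, Secondary objectives, Table 3, the fNIRS section or the Discussion |
| Eight coping scores | Improvement, only through the psychosocial domain (Abstract; Table 3 places coping there) | Effects | Not stated in Table 3 or the questionnaire section |

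**3. Error rate per test.** The two-group ANCOVA F test has one numerator degree of freedom and gives a two-sided p-value. A one-sided p-value is half of that when the estimate has the pre-stated sign.
- Sign fixed in advance: false-positive rate = 0.05.
- Either sign accepted at one-sided 0.05: 0.05 + 0.05 = 0.10, the same as rejecting at two-sided p ≤ 0.10.

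**4. Illustration for the eight coping scores at one visit** (no alpha-adjustment, independence assumed; eight subscales of one questionnaire will in fact be correlated). Chance of at least one false benefit when there is no true effect:
- Signs fixed: 1 − 0.95^8 = 0.34.
- Signs open: 1 − 0.90^8 = 0.57.

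The 0.34 is ordinary multiplicity. Only the step from 0.34 to 0.57 comes from the open sign.

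**5. Does alpha-adjustment remove it?** No. If the adjusted one-sided level is a, accepting either sign gives 2a. As an example (the article names no method), Bonferroni over eight scores gives a = 0.05 / 8 = 0.00625 and 2a = 0.0125, so the bound for the family is 8 × 0.0125 = 0.10 instead of 0.05.

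**6. Price of two-sided testing.** With 80 degrees of freedom, the critical t rises from 1.664 (one-sided 0.05) to 1.990 (two-sided 0.05). The smallest difference that reaches significance grows by 1.990 / 1.664 = 1.20, about 20%.

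**The case against.** **The objectives are already neutral.** They speak of changes and effects, and the predictions stand only in the Abstract and Background. This is true, and it shows that part of the remedy is wording. It does not repair the analysis section, where the one-sided level is set for all outcomes.

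**Direction and contrast definitions belong in a statistical analysis plan, and the cited fNIRS and questionnaire sources may settle them.** Neither is available here, and mere absence of such detail would be no finding. But the article itself fixes a one-sided rule, and that rule cannot be carried out for these outcomes on what the article states.

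**Coping is weakly covered by the prediction.** This stands. Kinesiophobia is the only psychosocial example in the Abstract. The Background also links passive coping to chronic back pain, so an unfavourable direction can be guessed for a scale such as catastrophizing, but no scale is mapped.

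Several stronger readings are tempting and are not supported:
- *No result could count against MultiMove.* A null result could. Nor does the article say that the sign will be chosen after the data are seen; it only leaves that open.
- *Efficient activation cannot be told from giving up on the counting.* Table 3 groups the prefrontal response, gait, sway, dual task costs and correct calculations in one construct. The analysis section plans further analyses of outcomes and their interactions plus exploratory mediation, and the Discussion intends a combined reading. No formal rule is given, but joint interpretation is planned.
- *The error is huge across the set.* Oxy- and deoxyhaemoglobin in two dual tasks plus eight coping scores are 12 outcomes, or 24 tests at two visits, with 1 − 0.95^24 = 0.71 against 1 − 0.90^24 = 0.92. The 0.71 has nothing to do with direction, independence is implausible for paired signals, related subscales and repeated visits, and the promised adjustment is left out.

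**Conclusion.** The point holds for these secondary outcomes only. The article applies a one-sided level to the prefrontal haemodynamic response and the eight coping scores without saying which direction is favourable, so the rejection region is undefined. If either sign may count as benefit, the per-test false-positive rate is 0.10 rather than the nominal 0.05, before alpha-adjustment, and adjustment alone leaves the doubling in place. The size rests on one condition, that the sign stays open until the results are known; if directions are fixed beforehand, the excess disappears. The support is firmer for the prefrontal response, where improvement is predicted by name, than for coping. The Timed Up-and-Go analysis and the total of 100 participants are untouched by this point.

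**What to change.** In Data analysis and management, state that the prefrontal haemodynamic outcomes and the eight coping scores are tested two-sided at 0.05 and reported as changes. Keep a directional claim only for an outcome whose favourable direction is stated before the data are seen; a short table would do, with one line for oxy- and one for deoxyhaemoglobin per task and one line per coping score. Bring the improvement wording in the Abstract and Background into line with the neutral Secondary objectives.

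The cost is small: no new data and no more participants. The threshold for these outcomes becomes stricter (critical t about 1.99 instead of 1.66), and some results can only be reported as changed.

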## Methods

### Study design and setting

The current study is designed as a prospective, two-arm randomized, controlled, superiority clinical trial. To assess the effect of MultiMove on the measures presented above in CLBP patients, subjects will be allocated to an intervention group (IG) or a control group (CG) using block randomization (1:1 allocation) [47]. The primary and secondary outcomes will be assessed at three time points (see Fig. 1, a detailed overview of the outcome measures can be found in Table 3).

**Fig. 1 Fig1:**
[figure not shown]
Study schedule of enrolment, intervention and assessments

The first measurements will be conducted directly before intervention onset (baseline), the second directly after the intervention (post, week 12–14, t1), and the third after additional 12 weeks (follow-up, week 24–26, t2). All investigators will be blinded to group allocation. Data collection will be performed at the Otto von Guericke University (OvGU) Magdeburg (Germany). The protocol is in line with the principles of the Declaration of Helsinki and was approved by the institutional review board (IRB) of the OvGU (registration number: 182/18).

### Study population and eligibility criteria

MultiMove is designed for outpatients with CLBP associated with degenerative diseases of the lumbar spine and aged ≥50. They will be recruited by the orthopaedic department of the Klinikum Magdeburg gGmbH in collaboration with local orthopaedist. Information will be provided in written form in doctor’s practices as well as personally in their consultations. In addition, the study will be advertised via local newspaper.

To be considered for the study, participants must comply all off the following inclusion criteria:
(i)age ≥ 50 years(ii)an average low back pain over the last 4 weeks ≥4 on a numerical rating scale (NRS) from 0 - no pain to 10 - pain as bad as it could be(iii)duration of LBP and/or neurogenic claudication ≥3 months(iv)International Classification of Diseases 10th revision diagnosis code related to chronic back pain (ICD-10: M54 Dorsalgia; M48.0 Spinal stenosis; M54.5 Low back pain; M54.4 Lumbago with sciatica; M54.1 Radiculopathy; M41.5 Other secondary scoliosis; M43.1 Spondylolisthesis; M42.1 Adult osteochondrosis of spine; M51.2 Other specified intervertebral disc displacement; M47.8 other spondylosis; M53.2 Spinal instabilities)

Exclusion criteria are: (i) more than two prior operations of the spine, (ii) spinal fusion of more than three segments, (iii) any spinal operation within the last 6 months, (iv) dependence on a walking aid or inability to walk more than 300 m at a stretch, (v) reduction in strength of more than 25% according to Janda [48] (level 0–3), (vi) congenital spine deformities, (viii) any neurological, cardiovascular, psychological and musculoskeletal diseases that preclude the execution of the intervention and the measurements.

### Sample size

Sample size was calculated using G*Power (version 3.1.9.7.). Because previous studies have shown large effect sizes for changes in the TUG performance after single interventions (dancing [49], strength training [50]) as well as after multimodal interventions [51] in healthy older adults, a large effect size (f = 0.40) was assumed for the sample size calculation. Considering an α level of 0.05, a power of 0.95, two groups and two covariates (baseline scores and, when required, e.g. age, sex, etc.), the required total sample size for an analysis of covariance (ANCOVA) amounted 84 participants. With a hypothesized dropout rate of around 15%, a total sample size of 100 participants seems to be legitimated.

